### 2.7. Adverse Event Report

The investigator will report within 24 h any severe adverse events to the Principal Investigator (PI) regardless of whether they are related to the intervention during the trial. In addition, events considered serious by the investigator or that suggest significant risks, contraindications, side effects, or precautions that may be associated with the intervention will be recorded in the progress note as serious adverse events. In this study, the following are considered as severe adverse events: death: life-threatening events, the need for hospital admission or to extend the admission period, events resulting in continuous or severe disability or impairment of function, deformity or abnormality of the fetus.

When severe adverse events occur, the PI will notify the client (Daejeon Korean Medicine Hospital of Daejeon University) immediately and provide within five days an additional report containing detailed information. The trial should be halted until further instructions are provided. The client should promptly report any severe or unexpected adverse events including onset, severity, treatment taken, progress, or casualty to other relevant investigators, the Institutional Review Board (IRB), and the Director of the Ministry of Food and Drug Safety.

### 2.8. Criteria for Discontinuation or Dropout

#### 2.8.1. Discontinuation

If an adverse event or side effect occurs that negatively impacts either the safety of the subjects or the progression of the clinical trial, the ongoing trial should be discontinued. However, safety assessments related to the adverse event or side effect will still be conducted to ensure thorough evaluation and monitoring. The PI and the client will discuss the safety of the intervention and decide whether to proceed or discontinue the trial, and the decision is reported to the IRB and the Ministry of Food and Drug Safety.

#### 2.8.2. Dropout

Subjects will be dropped if they fail to complete the trial due to adverse events or other reasons. The investigator can stop the interventions and tests and drop the subjects from the trial, or the subjects can always drop out of the trial with their own free will. The subjects may be dropped in the following cases: severe adverse events occurred to the subjects; difficulty proceeding with the trial due to adverse events; discovering systemic disease that was not detected in the pre-intervention examination; the subject or a legal representative of the subject requests to stop the trial due to unsatisfaction; the subject does not comply with the instructions of the investigator; the subject withdraws consent to participate in the trial; the subject cannot be tracked to follow-up; the subject is prescribed a treatment that can affect the study result, without the direction or consent of the investigator during the trial period or follow-up period; progression of the trial is considered inappropriate by the investigator.

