Additional visits may be made at any time other than the scheduled visit when deemed necessary at the request of the subject or discretion of the researcher. If a subject visits on an unscheduled day, adverse reactions, concomitant medications, results of tests performed, and subsequent medical treatment must be recorded in the case record. Even in the case of subjects who drop out, laboratory tests, pregnancy diagnostic tests, and efficacy evaluation tests can be performed during additional visits.

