#### 2.4.4. Randomization and Blinding

The people in charge of other assignments (or independent statisticians) who are not involved in conducting and evaluating this clinical trial will generate a random assignment list in a specific and reproducible manner. Randomization of experimental group 1, group 2, and the control group will be performed with a block randomization method in a 1:1:1 ratio. The random assignment table will be sealed and kept in a way that can be checked for unsealing, managed separately by the research manager in the presence of the participants. Each group will be randomly assigned with the same probability of each individual being selected using the statistical program StataMP 16 program (StataCorp LLC, [name]). The investigators and assessors will be separated so that the assessors will not know what kind of treatment the subjects have received. It is not possible to maintain investigator blindness.

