#### 2.6.2. Prohibited Drugs

There are no specific drugs prohibited from concomitant use, but the drugs that may affect results can be prohibited at the discretion of the researchers’ decision (e.g., starting with new medications, such as anti-depressants, anti-anxiety drugs, anti-psychotics, corticosteroids, female hormones, L-dopa, digitalis, bromide, cyclosporin, disulfiram, isoniazid, and yohimbine, during the clinical trial). Participants will be required to maintain a stable treatment regimen throughout the study period. Initiation of any new treatments, including additional medications or therapeutic interventions outside of the ETE, will result in withdrawal from the study. This criterion is intended to isolate the effects of the ETE intervention on Hwa-Byung symptoms and prevent confounding results from other treatments.

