### 2.9. Compliance Assessment

Compliance assessment will be performed as follows:$$Compliance\left(\%\right)=\frac{Number\;of\;performed\;interventions}{Number\;of\;planned\;interventions}\times 100$$

Compliance (%) during the trial should be at least 75%. If the compliance (%) of the subjects is less than 75%, it is considered poor and is excluded from the Per-Protocol (PP) analysis.

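### Dropout rules let assessments stop with the intervention and leave later outcome collection optional, so the week-8 HB-M may be missing for subjects who stop early

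*Protocol article*

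**What the plan says.** Section 2.8.2 (Dropout) joins three acts in one permission: "The investigator can stop the interventions and tests and drop the subjects from the trial". Among the grounds on which a subject may be dropped are that "the subject does not comply with the instructions of the investigator" and that "progression of the trial is considered inappropriate by the investigator". Adverse events, dissatisfaction, withdrawn consent and loss to follow-up are also listed. Section 2.4.4 says of the person who takes the discretionary decisions: "It is not possible to maintain investigator blindness". Only assessors are blinded.

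Section 2.6.2 adds a rule without discretion: starting a new treatment outside the trial therapy "will result in withdrawal from the study".

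The one provision for outcomes after dropout is the paragraph on additional visits in Section 2.2: "Even in the case of subjects who drop out, laboratory tests, pregnancy diagnostic tests, and efficacy evaluation tests can be performed during additional visits". Those visits take place when the subject asks or the researcher thinks them necessary, and they carry no week-8 date.

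The primary outcome (Section 2.11.1) is the HB-M change from baseline to week 8. Section 2.2 schedules HB-M at visit 1, visit 12 (week 8) and visit 13 (week 16). Visit 8 collects only EQ-5D, EQ-VAS and costs.

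**The concern.** The primary analysis is on the FAS, which is meant to keep subjects in the comparison whether or not they finish treatment. That needs a week-8 score from subjects who stop. The protocol defines no status of off the intervention but still assessed, and it makes later measurement a matter of choice.

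The reasons for leaving are unlikely to be the same in each arm. Controls receive materials and wait, so they have no sessions to miss or to react to, and intolerance of a headset can arise only with VR-based ETE. Controls who do poorly may instead look for other treatment and be withdrawn under Section 2.6.2. Every pairwise contrast on the primary outcome could be affected, and the EQ-5D and cost follow-up would be cut short in the same subjects.

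**Working it through.** **1. Can a subject lack any post-baseline HB-M?** Yes. Suppose a subject is dropped in week 3. Visit 12 is not yet due, visit 8 has no HB-M, and visits 12 and 13 fall away if tests stop. The only remaining source is an optional extra visit (Section 2.2). Section 2.11.1 then calls for imputation, by a method chosen after the amount and mechanism of missingness have been examined. Alternatively, a subject with no evaluation at all since randomisation leaves the FAS under Section 2.10. The per-protocol set excludes dropouts in any case.

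**2. How many subjects?** Section 2.4.3 plans for 25% dropout with 32 per group: 0.25 × 32 = 8 per group, or 24 of 96, leaving 24 measured per group if all of it falls before week 8.

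**3. The plan's own sample-size figure.** n = 2·SD²·(1.96 + 0.84)²/Δ².
- Formula inputs (SD 6.9, Δ = 7.8 − 2.8 = 5.0): 2 × 6.9² × 2.8²/5.0² = 29.86, so 30 per group, as printed.
- Text inputs (SD 5.178, Δ = 6.84 − 2.52 = 4.32): 22.53, so 23 per group.
- Dropout step: 30/0.75 = 40, not 32; 23/0.75 = 30.7, so 31, close to 32.

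The mismatch between the two sets of inputs is a separate matter. Both sets are carried forward here.

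**4. Precision at stake.** Power ≈ Φ(Δ/(SD·√(2/n)) − 1.96).

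| Measured per group | Text inputs (4.32; 5.178) | Formula inputs (5.0; 6.9) |
|---|---|---|
| 24 | Φ(2.89 − 1.96) = 0.82 | Φ(2.51 − 1.96) = 0.71 |
| 32 | Φ(3.34 − 1.96) = 0.92 | Φ(2.90 − 1.96) = 0.83 |

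**5. Bias, as an illustration.** Let a fraction d of an arm stop, and let g be the gap between the change imputed for them and their true change. The arm mean is then overstated by d·g, and the active-minus-control difference by d_A·g_A − d_C·g_C.

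Assume that active-arm stoppers end at the control-level change (g_A = 6.84 − 2.52 = 4.32), that they are imputed like completers, that 6.84 is a completer mean, that all stopping precedes week 8, and that the control arm contributes nothing (d_C·g_C = 0).
- d_A = 0.25: true difference 0.75 × 4.32 = 3.24; reported 4.32; overstated by 1.08 (1.08/3.24 = 33%).
- d_A = 0.125: true difference 0.875 × 4.32 = 3.78; overstated by 0.54 (0.54/3.78 = 14%).

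If controls who do poorly leave and are imputed like control completers, d_C·g_C is positive and offsets this. With equal d and g in both arms the net bias is zero, and with a larger control term it changes sign.

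**The case against.** The text is permissive. The investigator can stop tests and subjects may be dropped, but neither is required, and Section 2.2 says that "efficacy evaluation tests can be performed during additional visits". A reader might infer that the week-8 score is lost for everyone who stops. The documents support only that it may be lost. They also do not make every loss an unblinded decision: withdrawn consent and loss to follow-up are not the investigator's choice, and no wording would recover those scores.

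A reader might also see a contradiction between Sections 2.8.2 and 2.9. There is none. Section 2.9 sets a numerical threshold with a limited consequence: "If the compliance (%) of the subjects is less than 75%, it is considered poor and is excluded from the Per-Protocol (PP) analysis". Section 2.8.2 concerns not following instructions and says only that such a subject may be dropped. Section 2.10 lists dropout and low compliance as separate per-protocol exclusions, which implies that a poor complier can stay in the trial.

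Section 2.10 promises imputation suited to the reason for missingness, and a fuller protocol behind the article may fix the timing of assessments after dropout. The first point does not meet the concern, because no method can draw on an HB-M that was never taken. The second remains possible, but the article states a rule of its own on dropout, and that rule leaves collection optional.

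**Conclusion.** The point holds as a weakness in data collection that should be fixed. Three provisions combine: tests may stop together with the intervention, a new treatment ends participation, and later efficacy measurement is optional and undated. With no HB-M between visits 1 and 12, the primary outcome may be missing for subjects who stop early.

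The precision cost follows from the plan's own inputs if all 25% dropout precedes week 8, which Section 2.4.3 does not say. The 1.08 and 0.54 point figures are illustrations and should not be read as the expected bias. They rest on the five assumptions listed with them, and the cited source that would show whether 6.84 is a completer mean is not at hand. It is tempting to conclude that the bias favours ETE or VR-based ETE. The documents do not show this, since poorly doing controls can also leave through Section 2.6.2 and subjects may stop because they have improved.

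**What to change.** Reconcile Sections 2.2, 2.6.2 and 2.8.2 so that stopping the intervention and withdrawing from the study are two different events. State that subjects who stop the intervention or start another treatment, who have not withdrawn consent to follow-up and who can be reached, will have the week-8 (visit 12) and week-16 (visit 13) assessments by the blinded assessor, at the calendar dates counted from visit 1. In Section 2.2, replace the permission to test with that requirement. State in Section 2.10 or 2.11.1 that these observed scores enter the FAS. The change concerns assessments only and takes no position on the clinical grounds for stopping treatment.

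The cost is a protocol amendment with IRB approval and notice to participants (Section 2.17), and extra scheduling of one or two assessment visits for at most about 24 patients (25% of 96). The observed effect may also turn out smaller. Scores for subjects who have withdrawn consent or are lost to follow-up will still need imputation.

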### 2.9. Compliance Assessment

Compliance assessment will be performed as follows:$$Compliance\left(\%\right)=\frac{Number\;of\;performed\;interventions}{Number\;of\;planned\;interventions}\times 100$$

Compliance (%) during the trial should be at least 75%. If the compliance (%) of the subjects is less than 75%, it is considered poor and is excluded from the Per-Protocol (PP) analysis.

### 2.10. Statistical Analysis

Efficacy analysis will be evaluated primarily based on the Full Analysis Set (FAS) principle and secondarily according to the Per-Protocol (PP) principle of the primary outcome. Missing values will be imputed appropriately according to why they occur. Subjects are excluded from FAS analysis in following cases: failure to meet eligible criteria, no intervention specified in the clinical study plan has been received, no data have been collected because they have never been evaluated since randomization. Subjects will be excluded from the per-protocol (PP) analysis if they meet any of the following conditions: 1. Dropped out during the trial. 2. Violated the inclusion or exclusion criteria. 3. Had less than 75% compliance with the overall intervention. Additionally, other serious violations of the study protocol may also be considered as grounds for exclusion from the PP analysis. The demographic data of the study subjects included in this trial and baseline clinical history data will be presented with mean and standard deviation (SD) for continuous data for each group and frequency and percentage for categorical data. For each group, an independent sample t-test or Wilcoxon rank sum test will be performed depending on normality in the case of continuous variables, and for categorical variables, a Pearson chi-square test or Fisher’s practice test will be performed.

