### 2.5. Interventions

The ETE group (experimental group 1) and VR-based ETE group (experimental group 2) will receive ETE two times per week for the first four weeks and once a week for the next four weeks (a total of 12 times). The daily management group (control group) will receive Hwa-Byung management training materials and wait for eight weeks living a daily life. Hwa-Byung management training materials will be the same for the experimental and control groups.

ETE will be performed by a specialist in oriental neuropsychiatry or a resident who has been educated by a specialist in oriental neuropsychiatry and has over one year of clinical experience in neuropsychiatry of traditional Korean medicine.

We will follow the ETE protocol [17]. It consists of five stages: (1) assessment of emotion and physical symptoms (CSEI-S, Mentalizing the Room of Mind (MRM), SUDS); (2) analyze the relationship between emotion and physical symptoms, analyzing emotion and sensation with oriental neuropsychiatric perspective, and finding core emotion; (3) training—depending on the patient’s emotional state, choose from exposure mindfulness meditation, breathing meditation, somatic mindfulness meditation, upper danjeon meditation, joy meditation, lower danjeon meditation, middle danjeon meditation, resource mindfulness meditation, and integrated-triple danjeon meditation; (4) assessment of emotion and physical symptoms after intervention (CSEI-S, MRM, SUDS); and (5) managing emotion education.

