#### 2.11.2. Secondary Outcome

The secondary outcome will be assessed by changes in the HB-M score from baseline to 16 weeks, changes in the CSEI-S, PHQ-15, SRI, BDI, STAXI, and STAI from baseline to 8 and 16 weeks, and changes in the fNIRS and HRV from baseline to 8 weeks.

CSEI-S measures the core emotions of the patient in a clinical setting [38]. PHQ-15 assesses depression and physical symptoms [39]. SRI measures the degree of stress response [40]. BDI measures the current severity of depression, regardless of psychiatric diagnosis [41]. STAXI measures anger experiences and forms of anger expression [42]. STAI measures state anxiety and trait anxiety [43]. fNIRS shows prefrontal cortex activation which is prominent during both emotional processing and regulation [44]. HRV measures heart rate variability consistent with autonomic nervous system functional status [45].

We will use ANCOVA or baseline-variables-corrected multiple regression analysis for the efficacy assessment of the CSEI-S, PHQ-15, SRI, BDI, STAXI, STAI, fNIRS, and HRV variables. The baseline score will be used as a covariate, in which case a PP analysis will be performed without handling missing values.

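### The single, undated per-protocol rule can remove patients fully treated and measured at week 8 from week-8 results because of events between weeks 8 and 16

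*Protocol article*

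**What the plan says.** Section 2.10 lists the PP exclusions once, without reference to any visit: "Subjects will be excluded from the per-protocol (PP) analysis if they meet any of the following conditions: 1. Dropped out during the trial". The others are eligibility violations, compliance below 75% and, at discretion, other serious protocol violations.

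Section 2.8.2 says what dropout is: "Subjects will be dropped if they fail to complete the trial due to adverse events or other reasons". Two of its listed grounds reach past the treatment phase. One is that "the subject cannot be tracked to follow-up". The other is a prescribed treatment that could affect the result, taken "without the direction or consent of the investigator during the trial period or follow-up period". Section 2.6.2 adds: "Initiation of any new treatments, including additional medications or therapeutic interventions outside of the ETE, will result in withdrawal from the study".

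The 12 sessions end at week 8 (section 2.5), and the primary outcome is the HB-M change to week 8 (section 2.11.1). The last visit, visit 13, is at 16 weeks (section 2.2). Secondary outcomes include "changes in the CSEI-S, PHQ-15, SRI, BDI, STAXI, and STAI from baseline to 8 and 16 weeks"; fNIRS and HRV are analysed to week 8 only.

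For the primary outcome, section 2.10 puts the full analysis set (FAS) first and PP second. For the six scales, fNIRS and HRV, section 2.11.2 names a PP analysis in which missing values are not handled, and no other.

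**The concern.** Whether a patient belongs in a week-8 analysis should depend on what happened up to week 8. Under the rule as worded, it can depend on what happens in the eight weeks afterwards. Nothing in that later period can change the sessions already attended or the measurements already taken. The point is plainest for fNIRS and HRV, which are not measured after week 8 at all.

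Two things are at stake. First, valid week-8 data would be discarded. Second, if leaving after week 8 depends on both the week-8 result and the arm, the remaining patients are a selected group. Controls receive training materials and "wait for eight weeks living a daily life". Those still unwell at week 8 might be more likely to start another treatment, which section 2.6.2 turns into withdrawal. That tendency is an inference; the article does not state it.

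**Working it through.** **Does the rule reach past week 8?** Take a patient with 12 of 12 sessions (compliance 12/12 × 100 = 100%), all week-8 measures taken, and loss to follow-up at week 10. Under section 2.8.2 this patient has not completed the trial and meets a listed dropout ground. Under section 2.10 the patient then meets the first PP exclusion. No sentence restores the patient to the week-8 set. The FAS exclusions (ineligible, no intervention received, never evaluated after randomisation) do not apply, so the patient stays in the main HB-M analysis.

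**How many patients?** Section 2.4.3 plans 32 per group and 25% dropout: 32 × 0.25 = 8 dropouts, leaving 32 − 8 = 24. The article does not say when dropout occurs, so let *f* be the share after week 8 (an assumption, equal across arms). The rule as written leaves at most 24 per arm. A week-8 set defined by events up to week 8 leaves up to 24 + 8*f*.

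**Power.** The plan's own sample-size formula, 2 × 6.9² × 2.8² / 5.0², gives 29.86, so 30 per group as printed. The prose in the same section gives other inputs: a difference of 6.84 − 2.52 = 4.32 and an SD of 5.178. That mismatch is a separate matter, so both sets are shown. Power for one two-arm HB-M comparison, two-sided 5%, is Φ(Δ / (SD × √(2/n)) − 1.96). Example, n = 24, prose inputs: 5.178 × √(2/24) = 1.495; 4.32/1.495 = 2.890; Φ(0.930) = 0.82.

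| Share of dropout after week 8 | Measured patients discarded per arm | Week-8 PP set by time point | Power, prose inputs | Power, printed-formula inputs |
|---|---|---|---|---|
| 0% | 0 | 24 | 0.82 | 0.71 |
| 25% | 2 | 26 | 0.85 | 0.74 |
| 50% | 4 | 28 | 0.88 | 0.77 |
| 75% | 6 | 30 | 0.90 | 0.80 |
| 100% | 8 | 32 | 0.92 | 0.83 |

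The first row is also what the rule as written gives throughout. Set sizes are upper limits, because the compliance and eligibility exclusions also apply.

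**Possible shift of the control mean (illustration only).** Assume half the planned dropout falls after week 8, so 4 of 32 controls (p = 0.125) leave late. Assume that their propensity to leave has correlation *r* with a poor week-8 change, and that the active arms have no such selection. The shift is r × SD × φ(z_p)/(1 − p). With z = −1.150 and φ(z) = 0.206, φ(z)/(1 − p) = 0.206/0.875 = 0.235, and 5.178 × 0.235 = 1.22.

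- r = 0.3: 0.3 × 1.22 = 0.37 points
- r = 0.5: 0.5 × 1.22 = 0.61 points

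Taking the 4 as a share of the 28 controls then still measured (p = 4/28 = 0.143) gives a factor of 0.226/0.857 = 0.263 and shifts of 0.41 and 0.68, the same order of size. Similar selection in the active arms would reduce the effect on the difference.

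**The case against.** The strongest reply is that the trial, in the PP rule, means the eight treatment weeks. Section 2.9, immediately before it, speaks of compliance over the trial, and sessions occur only in weeks 0 to 8. Section 2.12 compares laboratory results before and after the trial; section 2.2 schedules those tests at screening and visit 12 and lists none at visit 13. Section 2.8.2 itself sets a trial period beside a follow-up period. On this reading nobody measured at week 8 is removed for later events. This stands as a possible reading. It does not settle the matter, because section 2.8.2 also treats follow-up events as dropout and section 2.10 sets no limit.

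Nor is the narrow reading unworkable at week 16. A patient without a week-16 score falls out of an analysis that does not handle missing values, and outside treatment during follow-up could count as a serious violation. It would be too strong to say that one rule must fail at one of the two time points; the fault is that the text does not say which period it means.

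It can also be said that visit-specific analysis sets are usually left to the analysis plan. That is fair for omitted detail. Here, though, the article lists the PP criteria, and an analysis plan that follows them inherits the ambiguity.

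Finally, the bias described is not established. It needs leaving to depend on arm and outcome. In the direction suggested, it would flatter the controls and so understate the active-versus-control difference. No asymmetry is apparent for ETE against VR-based ETE, the comparison in the stated aim. All of this stands.

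**Conclusion.** The point holds as a fault in a stated rule. The PP exclusion carries no time point, and read together with section 2.8.2 it removes treated and measured patients from week-8 PP results because of later events. That reading is probable, not certain.

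The reach is limited. A reader might infer that the primary result is at risk; it is not, since the FAS analysis of week-8 HB-M keeps these patients. The exposed results are the supporting PP analysis of HB-M and the week-8 analyses of CSEI-S, PHQ-15, SRI, BDI, STAXI, STAI, fNIRS and HRV.

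The size rests on unstated dropout timing: 0 to 8 measured patients per arm discarded at 25% dropout and, for HB-M on the prose inputs, power of about 0.82 instead of up to 0.92. The article gives no inputs to size the effect on the secondary measures.

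A reader might also infer a bias worth a large part of the assumed 4.32-point difference. With complete selection (r = 1) the control shift would be 1.22 points (1.22/4.32 = 28%), but nothing in the article supports such selection, or its absence in the active arms. The 0.37 to 0.61 points at r = 0.3 to 0.5 only illustrate the mechanism.

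**What to change.** In section 2.10, define PP membership per time point, using only events up to that assessment:

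- **Week-8 PP set:** eligible, compliance at least 75%, no dropout before the week-8 assessment, regardless of anything later.
- **Week-16 PP set:** the same, plus no dropout before the week-16 assessment.

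Use the week-8 set for every week-8 PP analysis, including fNIRS and HRV, and the week-16 set for week-16 PP analyses. The existing provision on other serious violations should be tied to the same cut-offs.

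The cost is a short rewording of section 2.10 and one extra analysis-set flag. It needs no additional patients, visits or data, and should be settled before outcome data are examined.
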